### Methods to reduce bias and enhance data quality

With reference to the Cochrane Collaboration’s tool for assessing risk of bias [23], a number of procedures are carried out to reduce potential sources of bias. Firstly, to reduce selection bias, participating GP practices in both states are recruited with identical procedures. A non-responder analysis will also be performed. Secondly, randomization of participating practices will be performed electronically by statisticians not involved in physician recruitment. Thirdly, specified inclusion and exclusion criteria (ICD and ATC codes) will be used to calculate antibiotic prescription rates for ARTI among participating practices in order to reduce the risk for information bias and selective outcome reporting. Fourthly, to reduce variation in intervention delivery, outreach visits will be standardized. Due to financial and time constraints within this trial it will not be possible to blind participants and trial staff. Prior to its start, the study was registered in the public trial archive ISRCTN.

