### Recruitment

GP practices will be recruited in the two German states, Mecklenburg-Western Pomerania (MV) and Baden-Wurttemberg (BW). A total of 114 practices will be included in the trial (38 GPs in MV and 76 GPs in BW). GPs will be approached via invitation letters. Interested physicians will receive trial information via telephone or during a practice visit. Participating GPs will provide informed consent in writing. They will also agree to release their patients’ anonymized prescription data as stored by the German statutory health insurance provider AOK (§§295, 300 SGB V). These data include all AOK-insured patients diagnosed with ARTI who receive medical treatment during the trial. Using these data, overall and practice-specific antibiotic prescription rates will be determined.

In addition, two written patient surveys will be conducted over two successive winter seasons. In each survey participating GP practices will recruit up to 50 ARTI patients aged 17 years or over to fill in a questionnaire. The questionnaire will measure patients’ knowledge of antibiotics as well as expectations and experiences related to antibiotic prescribing. Patients’ participation in the survey will be anonymous and not related to any affiliation with a specific health insurance provider. Exclusion criteria are: not being able to read or fill in the questionnaire.

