### Intervention

The intervention is multifaceted and includes different elements (Additional file 2). The IG will receive feedback on practice-specific antibiotic prescription on two occasions (Additional file 2, component 1) and an educational outreach visit (Additional file 2, component 2), which is a central focus of the intervention. During the visit, a specially trained expert will discuss the practice-specific antibiotic-prescription feedback provided in detail. Additionally, the practice will have access to e-learning modules focusing on communication strategies, e.g., on how to handle patients expecting the prescription of antibiotics (Additional file 2, component 3 and 4). Patient information on the common cold, middle ear infections, and sinus infections is tailored to different groups of patients, e.g., the elderly or parents of children with ARTI, and is provided in the form of flyers and information on tablet computers (Additional file 2, components 5 and 6). Communication designers will be involved in the development of the materials.

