### Sample size calculation

We expect to find a relative reduction of the antibiotic prescription rate of 30% (which means an absolute reduction from 40 to 28%) between the groups. The sample size considerations are based on the chi-squared test using a significance level of α = 5% (two-sided) and a power of (1 − β) = 80%. This results in a sample size of *n* = 244 patients per group. To take the clustered structure into account, we assumed an intra-cluster correlation coefficient (ICC) for patients in practices of 0.2 [24]. This value is based on previous studies. The cluster size is assumed to be *m* = 80 patients. Thus, the design effect (*DE*) equals *DE* = 1 + (*m* − 1) × *ICC* = 1 + 79 × 0.2 = 16.8. These considerations result in a sample size of *N* = *n* × *DE* = 244 × 16.8 = 4100 patients per group. Thus, the total sample size is 104 practices of size *m* = 80 resulting in 8320 patients. A drop-out rate of about 8% is expected and, therefore, 10 additional practices will be recruited (see Fig. 2 for detailed information on the scheduled flow of patients). The analysis will be done by using a logistic mixed-effects model, which we expect to explain more of the variance in the prescription of antibiotics. Therefore, the model should be more powerful than the chi-squared test. The calculations are done using SAS 9.4 (Proc Power).

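### The primary rate counts only patients whom unblinded GPs code as ARTI after randomisation, so differential coding or consulting could shift it; the fixed code lists do not prevent this, and a supportive check is needed

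*Protocol article*

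**What the plan says.** Under Outcome measures, the primary outcome is the GPs' antibiotic prescription rate for ARTI, taken from AOK claims, with ARTI defined by the ICD-10 codes in Table 2. Under Recruitment, the data released are described thus: "These data include all AOK-insured patients diagnosed with ARTI who receive medical treatment during the trial". Under Data collection, completeness and quality, outcome data are drawn from two winter seasons (T1 and T2), and the intervention begins once baseline (T0) has been collected.

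Under Intervention: "The IG will receive feedback on practice-specific antibiotic prescription on two occasions". The results are discussed at an outreach visit. Control practices provide usual care.

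Under Methods to reduce bias and enhance data quality, the article concedes that "it will not be possible to blind participants and trial staff". The same section offers the code lists as a safeguard: "specified inclusion and exclusion criteria (ICD and ATC codes) will be used to calculate antibiotic prescription rates for ARTI among participating practices". The stated purpose is to lower the risk of information bias and of selective outcome reporting.

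Under Statistical analyses, the primary model is a logistic mixed model in the ITT population, with a random practice intercept and with patient age and gender as covariates. The sensitivity analyses are per-protocol and adjustment for the baseline practice rate.

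**The concern.** A patient counts in the primary rate only if the treating GP records a Table 2 code. At T1 and T2 that happens after allocation, by a GP who knows the arm and, in one arm only, has been shown the practice's own prescribing figures. Three mechanisms could move the rate while prescribing stays the same:

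- more untreated colds are given an ARTI code;
- treated patients are given a diagnosis outside Table 2 (pneumonia, for instance, is not among its indications);
- the mix of patients who consult changes.

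The first two lower the rate in the intervention arm. The third could raise it if patient information leads mildly ill people to stay away.

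Fixed lists address a different problem, namely later choice of codes by analysts. ITT keeps practices in their allocated arm but does not make patients selected after allocation comparable. Neither described sensitivity analysis deals with a denominator that shifts by arm. The stake is interpretation: the trial aims to reduce antibiotic use, and a lower ratio does not by itself show that.

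**Working it through.** **Inputs from Sample size calculation.** "significance level of α = 5% (two-sided) and a power of (1 − β) = 80" per cent; an "absolute reduction from 40 to 28" per cent; "we assumed an intra-cluster correlation coefficient (ICC) for patients in practices of 0.2"; "The cluster size is assumed to be *m* = 80 patients".

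**The plan's own figure.** With pooled variance and no continuity correction,

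n = [1.96·√(2·0.34·0.66) + 0.8416·√(0.40·0.60 + 0.28·0.72)]² / 0.12² = 243.4, rounded up to 244 per group.

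Design effect = 1 + 79 × 0.2 = 16.8. Then 244 × 16.8 = 4099.2, stated as 4100; 4100/80 rounds up to 52 practices per arm, so 104 practices and 8320 patients. 104/(1 − 0.08) rounds up to 114. Everything reproduces, and the sample size is not at fault.

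**Coding shift.** At 40% of 80, a practice has 32 treated and 48 untreated ARTI patients. Let *o* be the share of treated patients coded outside Table 2, and *i* the relative increase in untreated patients given an ARTI code. With true prescribing unchanged,

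rate = 32(1 − o) / [32(1 − o) + 48(1 + i)].

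The documents give no value for *o* or *i*; those below are assumptions.

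| o | i | Calculation | Rate | Relative reduction |
|---|---|---|---|---|
| 0 | 10% | 32/84.8 | 37.7% | 6% |
| 0 | 20% | 32/89.6 | 35.7% | 11% |
| 0 | 30% | 32/94.4 | 33.9% | 15% |
| 5% | 5% | 30.4/80.8 | 37.6% | 6% |
| 10% | 10% | 28.8/81.6 | 35.3% | 12% |
| 20% | 20% | 25.6/83.2 | 30.8% | 23% |

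The target is 28%, a relative reduction of 30%.

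**Shifts needed for a given share of the target.**
- Half the target (34%): 32/0.34 − 80 = 14.1 extra untreated patients (29.4% more untreated); or (32 − 27.2)/0.66 = 7.3 treated patients moved off the list (22.7% of treated); or 12.8% each way.
- Full target (28%): 34.3 extra untreated (71.4% more), or 13.3 treated moved (41.7%), or 26.3% each way.

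**Effect on the test.** At the plan's ICC and size, effective n = 4160/16.8 = 247.6 per arm. By the chi-squared approximation, an artefactual fall to 37%, 36% or 34% would be declared significant about 10%, 15% or 28% of the time, against a nominal 5%.

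**What a count comparison would show.** If only untreated codes rise by 20%, the count goes from 80 to 89.6, which is 12% more. With 20% each way it goes to 83.2, only 4% more, although the rate falls to 30.8%. A count comparison therefore sees one-way inflation but can largely miss offsetting shifts.

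**The case against.** **Size.** A reader might infer that a coding shift alone would plausibly deliver most of the target effect. The documents do not support that: they give no figure for any shift and describe no payment or penalty tied to the rate. A shift of 5% each way yields about a fifth of the 12-point target (2.4/12), and the full target needs large shifts. The percentages also depend on their base. Adding 10%, 20% or 30% of all 80 coded patients gives 32/88 = 36.4%, 32/96 = 33.3% or 32/104 = 30.8%, but these are 16.7%, 33.3% and 50% more untreated patients. This objection stands as to size; the mechanism remains.

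**Direction.** A bias in favour of the intervention is likely but not certain, because informed patients with mild illness may consult less. This stands. It supports checking the denominator rather than presuming a direction.

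**Detectability.** The released data already contain ARTI-coded patients per practice, so inflation of the denominator can be examined without new data. This stands in part, since no such comparison is described and shifts to unlisted codes would be hard to see.

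**The bias statement.** The article says the lists reduce the risk of bias, not that they remove it. That is right, and the lists do help against selective reporting. The sentence is incomplete on information bias rather than wholly false.

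**Left to the analysis plan.** Supportive analyses may appear in a plan that is not shown, and their absence from the article is not the point here. The scope of the data release and the bias statement are both fixed in this article, and an analysis plan cannot use totals that were never requested.

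**Feedback content.** That the feedback reports this same ARTI rate is inferred from Recruitment and Intervention; Additional file 2 is not shown.

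**Conclusion.** The concern holds in limited form. The primary denominator is formed after allocation by unblinded GPs, only one arm receives prescribing feedback, and the code lists do not protect against coding that differs by arm. The rate could therefore move without any change in prescribing. Under the assumed shifts of 10% to 30% more untreated codes, or 10% to 20% each way, the spurious relative reduction is 6% to 23% against a 30% target. These figures illustrate sensitivity; they do not estimate bias. They rest on the plan's 40% rate and 80 patients per practice, and on shifts confined to the intervention arm. The documents do not show that such shifts will occur, that they must favour the intervention, or that they would be undetectable. The case is for an inexpensive supportive check, not for replacing the endpoint.

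**What to change.** 1. Pre-specify a comparison by arm of ARTI-coded patients per practice at T1 and T2, adjusted for T0. The data are already requested, so the cost is one practice-level model.
2. Ask AOK for practice-level aggregate totals at T0, T1 and T2, and add a supportive model, adjusted for T0, of J01 prescriptions per 1000 AOK patients of the practice. Preferably fix the patient denominator at baseline, so that it cannot respond to allocation. Exclude the urinary agents in Table 1 (nitrofurantoin, fosfomycin, trimethoprim) to limit dilution by non-ARTI use. Report the estimate with its confidence interval and use it to interpret the primary result, not as a pass/fail rule; some dilution will remain.
3. Confine the code-list sentence under Methods to reduce bias and enhance data quality to selective outcome reporting, and state that differential coding by arm remains possible.

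The cost is a slightly wider data request and possibly a change to the GP consent wording.

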### Sample size calculation

We expect to find a relative reduction of the antibiotic prescription rate of 30% (which means an absolute reduction from 40 to 28%) between the groups. The sample size considerations are based on the chi-squared test using a significance level of α = 5% (two-sided) and a power of (1 − β) = 80%. This results in a sample size of *n* = 244 patients per group. To take the clustered structure into account, we assumed an intra-cluster correlation coefficient (ICC) for patients in practices of 0.2 [24]. This value is based on previous studies. The cluster size is assumed to be *m* = 80 patients. Thus, the design effect (*DE*) equals *DE* = 1 + (*m* − 1) × *ICC* = 1 + 79 × 0.2 = 16.8. These considerations result in a sample size of *N* = *n* × *DE* = 244 × 16.8 = 4100 patients per group. Thus, the total sample size is 104 practices of size *m* = 80 resulting in 8320 patients. A drop-out rate of about 8% is expected and, therefore, 10 additional practices will be recruited (see Fig. 2 for detailed information on the scheduled flow of patients). The analysis will be done by using a logistic mixed-effects model, which we expect to explain more of the variance in the prescription of antibiotics. Therefore, the model should be more powerful than the chi-squared test. The calculations are done using SAS 9.4 (Proc Power).

**Fig. 2 Fig2:**
[figure not shown]
Flow chart of the CHANGE-3 trial

### Statistical analyses

In a first step, descriptive statistics will be provided for the primary and secondary outcomes as well as for patient, practice, and GP characteristics, including mean, standard deviation, median, interquartile range (IQR), minimum and maximum for continuous variables, and frequency in percentages for categorical variables. The primary objective of this study is to examine the difference in antibiotic prescription rate after intervention (T1) between the two study arms.

The confirmatory analysis of the primary endpoint will be conducted based on the intention-to-treat (ITT) population, where all patients will be included in the analysis and assigned to the group they were randomized to.

A logistic mixed-effects model will be applied to assess the respective hypothesis of equal rates in both groups regarding the primary endpoint using a significance level of α = 5%. A random intercept will be included for practices. Furthermore, age and gender of patients will be included as covariates. Missing values regarding the primary endpoint will be imputed using multiple imputation. As a sensitivity analysis, the primary endpoint will be evaluated on the per-protocol population, where patients with major protocol violations will be excluded. As a further sensitivity analysis, the baseline prescription rate on practice level will be included as an additional covariate in the primary logistic mixed-effects model.

Mixed models, as described for the primary endpoint, will be used to analyze the secondary outcomes. All calculated *p* values regarding secondary endpoints will be of a descriptive nature. A detailed statistical analysis plan will be written prior to the final analysis. SAS (SAS Institute Inc., Cary, NC, USA) version 9.4 or higher will be used to carry out the analyses. A non-responder analysis is planned regarding size of practice, number of antibiotic prescriptions in case of ARTI, and application of broad-spectrum antibiotics.

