### Randomization

Participating GP practices will be randomly assigned in a 1:1 ratio into the two study groups after recruitment. Randomization will be stratified by rate of antibiotic prescription for ARTI at baseline per practice. Randomization will be performed by the Institute of Medical Biometry and Informatics at the University Hospital Heidelberg.

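### The confirmatory model omits the practice-level baseline prescribing rate on which randomisation is stratified; if that rate predicts later prescribing, the primary confidence interval is too wide and the test conservative

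*Protocol article*

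**What the plan says.** Under Randomization, the protocol article names one stratification factor: "Randomization will be stratified by rate of antibiotic prescription for ARTI at baseline per practice".

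Under Statistical analyses, the confirmatory model is a logistic mixed-effects model with a random intercept for practice, in which "age and gender of patients will be included as covariates". The baseline rate appears later in that section, and only as a sensitivity analysis: "the baseline prescription rate on practice level will be included as an additional covariate in the primary logistic mixed-effects model".

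Under Sample size calculation, the trial is sized on a chi-squared test inflated for clustering. The section then turns to the mixed model, "which we expect to explain more of the variance in the prescription of antibiotics", and concludes that "the model should be more powerful than the chi-squared test".

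**The concern.** Stratifying on baseline prescribing makes sense only if that rate is expected to predict prescribing after the intervention. If it does, stratification balances the arms on it, so the treatment estimate varies less from one randomisation to another. A model that leaves the factor out does not know this. It counts the variance explained by baseline as unexplained variation between practices, and the reported standard error exceeds the true spread of the estimate. The interval is then too wide and the test rejects too rarely under the null.

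Two further points follow:

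- The expected power gain is attributed to a model whose fixed covariates are patient age and gender. A random intercept accounts for between-practice variance but does not reduce it for a treatment allocated by practice. The covariate best placed to reduce it is the one left out.
- A sensitivity analysis that may be clearly more precise than the confirmatory one invites dispute if only one of them reaches significance.

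The Outcome measures section also describes the primary outcome relative to baseline data, yet the confirmatory model has no baseline term.

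**Working it through.** **Inputs from Sample size calculation.** Two-sided α of 5%, power 80%, "an absolute reduction from 40 to 28" per cent, ICC 0.2, m = 80 patients per practice, 104 practices before drop-out.

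**Step 1: the protocol's own figure.** With pooled variance and mean rate 0.34:

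n = [1.960 × √(2 × 0.34 × 0.66) + 0.842 × √(0.40 × 0.60 + 0.28 × 0.72)]² / 0.12² = 243.4, so 244 per group.

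Design effect = 1 + 79 × 0.2 = 16.8. Then 244 × 16.8 = 4099.2 (stated as 4100), and 4099.2/80 = 51.24, so 52 practices per arm and 104 in all. Allowing for 8% drop-out, 104/0.92 = 113.04, so 114. Every step reproduces. With 52 practices per arm the effective size is 52 × 80/16.8 = 247.6 per arm and power is 80.7%.

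**Step 2: what age and gender can add.** The variance of a practice mean is proportional to ICC + (1 − ICC)/m = 0.2 + 0.8/80 = 0.21. The between-practice share is 0.2/0.21 = 95.2%.

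- If patient covariates removed all within-practice variance and no between-practice variance, the variance factor would be 0.952 and the interval √0.952 = 0.976 times as wide. Power would be 82.5%.
- If they explained 2% to 20% of within-practice variance only (assumed), power would be 80.7% to 81.0%.
- If they also explained 5% to 10% of between-practice variance (assumed, and possible only if age and gender mix differs between practices), power would be about 83% to 85%.

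**Step 3: the effect of omitting the stratification factor.** The protocol gives no baseline to follow-up correlation and no number of strata, so both are assumed. The simulation had 104 practices of 80 patients, ICC 0.2 and four strata of the observed baseline rate. A linear model on practice rates was fitted with and without the baseline rate. Where a range is shown, it covers two sets of runs.

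| Latent correlation | Reported SE too large by, unadjusted | Type I error, unadjusted | Unadjusted CI wider than adjusted by | Power, unadjusted v adjusted |
|---|---|---|---|---|
| 0 | 0% | 5% | 0% | no difference |
| 0.3 | 0-5% | 4-5% | 4% | 81-82 v 84% |
| 0.5 | 10-12% | 3% | 13% | 82-83 v 89% |
| 0.7 | 27-28% | 1% | 33% | 87 v 96% |

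At 0.7, for example, the unadjusted analysis reported a mean SE of 0.0445 while the estimate's actual standard deviation was 0.0348 (0.0445/0.0348 = 1.28). With the baseline rate in the model, both were 0.0334. Adjusted type I error lay between 4.5% and 6.0% across settings, with a Monte Carlo standard error of about 0.3 points (4000 runs).

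**Step 4: check of the width ratios.** If the baseline rate also rests on about 80 patients, the observed correlation is roughly the latent one times 0.952, and the expected ratio is 1/√(1 − r²).

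- Latent 0.3: r = 0.286, ratio 1.04.
- Latent 0.5: r = 0.476, ratio 1.14.
- Latent 0.7: r = 0.667, ratio 1.34.

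These agree with the simulated 1.04, 1.13 and 1.33.

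**The case against.** The best defence is that nothing essential depends on this. The error is conservative, the simulated power of the unadjusted analysis stays above 80%, the adjusted model is already prespecified, and the sample size takes no credit for the hoped-for gain. All of that stands. It limits the seriousness of the point but gives no reason to prefer the less efficient model as confirmatory. An unseen SAP is no answer either, because the article itself fixes which model is confirmatory and which is sensitivity.

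Four stronger readings are tempting, and the documents do not support them:

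- **The power gain cannot occur.** Age and gender could add a little, and more if case mix differs between practices. Stratification itself also makes the estimate less variable. The protocol's wording is only an expectation. It is unsupported by the listed covariates, not impossible.
- **Most of the precision is thrown away.** This confuses the reported standard error with the real spread of the estimate. Because stratification already balances baseline, the unadjusted estimate's actual standard deviation exceeded the adjusted one by only about 2% at correlation 0.5 (0.0396 v 0.0389) and 4% at 0.7 (0.0348 v 0.0334).
- **Adjustment lifts power from 81% to 90% or 98%.** The factor 1 − r² gives those figures at observed correlations of 0.5 and 0.7, but the 81% ignores stratification. The fair comparison is between the two analyses of the same stratified trial, as tabulated, and it must include low correlations.
- **Region should be added as well.** It is not named as a stratification factor, and no calculation here supports adding it.

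The magnitudes also have a real limit: the simulations used practice rates, not the planned patient-level logistic mixed model. In a logistic model the conditional odds ratio itself changes with adjustment, so the width ratios are approximate on that scale.

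**Conclusion.** The point holds as a matter of efficiency and of correct standard errors, not of validity. The only stratification factor named is missing from the confirmatory model. If it predicts follow-up prescribing, the primary interval is too wide and the test conservative.

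The size depends on a correlation that the protocol does not give. The effect is nil at 0 and small at 0.3. At 0.5 the test's true level is about 3% and some 6 to 7 points of power are lost. At 0.7 the level is about 1% and about 9 points are lost. These figures assume four strata, ICC 0.2, 80 patients per practice and a practice-level analysis.

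The statement that the mixed model should outperform the planning test is not supported by age and gender, because about 95% of the relevant variance lies between practices.

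**What to change.** 1. In Statistical analyses, and in the SAP that the article says will precede the final analysis, make the logistic mixed model with the practice-level T0 prescribing rate plus patient age and gender the confirmatory analysis. Move the model without the baseline rate to the sensitivity analysis.
2. In Sample size calculation, replace the sentence on greater power with a statement that the 80% power is without baseline adjustment, and that any material gain is expected from adjusting for the baseline practice rate.

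The cost is about one degree of freedom out of roughly 100. No new data are needed, because the baseline rate must be known for every practice before stratified randomisation. The swap should be fixed before outcome data by arm are seen.
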